**Fig. 1 Fig1:**
[figure not shown]
Timeline for the SWEpap study

Blinding will not be possible for the nurse and parents during the procedures. Since only the infant’s face and pulse oximetry will be videotaped, the subsequent PIPP-R pain assessment and GSR measurements will be blinded using muted recordings. The parents’ participation in the study is voluntary and they are informed in advance that they can withdraw at any time without giving any reason.

## Methods: data collection, data analyses and management, data monitoring

### Data collection

Demographic data of the parent-infant dyad is registered before the procedure starts, including registration of potential music and singing activities during pregnancy for the parents in group 3. In all groups: before, during and after the procedure the infant will have a saturation probe attached to one foot making it possible to measure heart rate and oxygen saturation and electrodes measuring galvanic skin response on the other foot. The infant’s face and pulse oximetry values will be videotaped for later pain assessment with PIPP-R. An experienced midwife/nurse will perform the venipuncture. Venipuncture is routinely used in all hospitals in Swedish neonatal and postnatal care since it is considered less painful for the infant than heel lance [56]. A tourniquet using a soft cotton band is applied, the skin is disinfected, and a 21–23 Gauge needle is used for the blood sampling. The infant will be monitored until the treatment is concluded. In case of failed attempts, only the first venipuncture will be used in the study. In the breastfeeding condition, the midwife/nurse will make sure that the infant is latched and sucking well before the blood test is performed to safeguard the analgesic effect of breastfeeding. The infants’ behavioral responses to pain together with oxygen saturation and heart rate values are videotaped with two digital video cameras and will be assessed subsequently from the video films.

### Data analyses, management and monitoring

Methods for statistical analyses are chosen depending on scales of measurement and normal distribution. The data will be analyzed with descriptive and comparative statistics. Continuous variables that are normally distribute will be presented with mean and standard deviation and compared with t-test for two groups and ANOVA for multiple groups. For data that doesn’t fulfil those criteria we will use median with interquartile range and Mann-Whitney U-test or Kruskall-Wallis one way analysis of variance, respectively. Intention-to-treat will be used, including all randomized parent-infant dyads in the analysis. The division of group 2 into 2a and 2b, which is a nomenclature to distinguish breastfeeding from no breastfeeding, will be taken into account in the comparative analyses and differences between the two subgroups will be scrutinized. Cohens kappa will be used to calculate interrater reliability between PIPP-R scorers.

The data collected in the study is safely stored on a secure server at Örebro University. The project folder on the server is only available to the researchers in the project and is automatically backed-up. The principal investigator is responsible for the data monitoring, ensuring that the researchers in the study are carrying out the research according to the research protocol, ensuring intervention fidelity in the live parental lullaby singing via recurring spot checks with microanalysis of the live singing, ensuring the research is keeping to time and budget and that the research is being conducted ethically. The research group will meet regularly to ensure consistency. During the original development of the project proposal of the SWEpap-study, the research group consulted with parents with previous extensive experience of NICU care. These parents will continue to give feedback on demand.

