## Methods: hypothesis, participants, interventions, measures and outcomes

### Hypothesis

No previous research has assessed the efficacy of combined parent-driven pain management with SSC, breastfeeding and live parental lullaby singing in newborn infants during routine newborn metabolic screening. In this research study, “**P**arents **a**s **p**ain management in **Swe**dish neonatal care – **SWEpap**”, we hypothesize that parent-driven pain management such as SSC in combination with breastfeeding and live parental lullaby singing, will provide a more effective pain management during venipuncture in newborn infants compared to standard pain care initiated by health care professionals.

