### Study design

This is a multi-center, randomized controlled trial (RCT) with three parallel groups with the allocation ratio 1:1:1.

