### Outcomes

The primary outcome is infant pain expression measured with Premature Infant Pain Profile Revised (PIPP-R) [50], which is a pain assessment instrument that has also been translated into Swedish [51].

Secondary outcomes in the RCT are: a) changes in galvanic skin response (GSR) (area small peaks, area huge peaks, peaks per second, average rise time, average peak), which is obtained via three electrodes on the infant’s foot [52], b) parents’ rating of the infant’s pain, c) parents’ rating of their own stress during the procedure and d) parents’ rating of how beneficial the pain management they were involved in felt to them and their infant.

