### Sample size

No previous RCT has examined the effects of parent-driven pain management in newborn infants by combining SSC, breastfeeding and live parental lullaby singing. Based on previous studies using PIPP-R or its predecessor PIPP in pain alleviation projects, a difference of two PIPP-R points between standard care (group 1) and the full parent driven pain management (group 3) is considered clinically important. Based on those studies we also assume a standard deviation around 2 points. A power calculation sets the number of infants to include in the study to 63 in each group, with a power of 0.8 and a significance level set to 0.05 (www.clincalc.com). To compensate for possible dropouts, incomplete data, such as equipment malfunction or blood sample collection failure, 75 infants per group will be enrolled, making a total of 225 infants.

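### The analysis section does not tie the primary PIPP-R analysis to group 3 versus group 1, and lets observed normality decide whether means or ranks are compared

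*Protocol article*

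**What the plan says.** The Study design section describes "three parallel groups with the allocation ratio 1:1:1". Under Outcomes, "The primary outcome is infant pain expression measured with Premature Infant Pain Profile Revised (PIPP-R"). The Hypothesis section expects that skin-to-skin contact combined with breastfeeding and lullaby singing "will provide a more effective pain management during venipuncture in newborn infants compared to standard pain care initiated by health care professionals". The Sample size section uses the same contrast: "a difference of two PIPP-R points between standard care (group 1) and the full parent driven pain management (group 3) is considered clinically important". It adds that "we also assume a standard deviation around 2 points" and sets 63 infants per group, "with a power of 0.8 and a significance level set to 0.05", raised to 75 for losses.

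The section on data analyses, management and monitoring does not take up that contrast. It opens with "Methods for statistical analyses are chosen depending on scales of measurement and normal distribution". Normally distributed continuous variables are summarised by mean and standard deviation and "compared with t-test for two groups and ANOVA for multiple groups". Otherwise the summary is the median with interquartile range, and the test is Mann-Whitney or Kruskal-Wallis. The section says that the split of group 2 into 2a and 2b will enter the comparisons. It does not say which comparison of PIPP-R is primary.

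**The concern.** The trial has one question and one contrast that answers it. The stated analysis rule leaves two things open about that contrast.

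- **Which comparison decides.** With three randomised arms, the rule sends a comparison of all arms to ANOVA or Kruskal-Wallis. That test asks whether any arm differs from any other. It can be significant because of group 2 alone.
- **Which quantity is estimated.** Observed normality decides whether means or ranks are compared. PIPP-R is a bounded score (0 to 21), so a departure from normality is quite possible. The rank route gives no estimate of the mean difference in PIPP-R points, the scale on which the protocol defines clinical importance.

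At stake is the reading of the result. An omnibus result driven by group 2 could be taken as support for the combined package, or the trial could report a p-value without the effect estimate that its readers need.

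**Working it through.** **Inputs.** From the Sample size section: difference 2 points, SD about 2, power 0.80, significance level 0.05 (taken as two-sided, since the sidedness is not stated), 63 per group, 75 enrolled. Assumptions for the check: normal data, equal SD in all arms, and the arm means shown below in the order group 1, 2, 3, where a lower score means less pain.

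**1. The plan's own figure.** For two means, n per group = 2 × (1.960 + 0.842)² × (SD/difference)².
- With SD 2 and difference 2: 2 × 7.849 × 1 = 15.7, so 16 per group (about 17 with the t distribution).
- With a standardised difference of 0.5, for example 1 point with SD 2: 2 × 7.849 × 4 = 62.8, so 63.

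The stated 63 does not follow from the stated inputs; it matches a standardised difference of 0.5. That is a separate point. It matters here because a 1-point effect is the one for which 63 per group gives 80% power, so step 2 uses 1 point.

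**2. Does a significant omnibus test show that 3 beats 1?** The noncentrality of the F-test is λ = n × Σ(μᵢ − μ̄)² / SD². Take means (0, −1, 0), so that only group 2 is better.
- μ̄ = −1/3, and Σ(μᵢ − μ̄)² = 1/9 + 4/9 + 1/9 = 0.667.
- λ = 63 × 0.667 / 4 = 10.5.
- The critical F with 2 and 186 degrees of freedom at 0.05 is 3.04.
- P(F > 3.04 given λ = 10.5) = 0.829. Simulation of 100,000 trials also gave 0.829.

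So the omnibus test is significant in 83% of trials in which group 3 is no better than group 1.

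**3. Does a direct test of 3 versus 1 hold its error?** Yes. A single pre-named t-test had a simulated type I error of 0.051. In the step 2 scenario, requiring both a significant F-test and a significant 3 versus 1 test gave a false 3 versus 1 finding in 5.0% of trials.

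**4. Does choosing the test by normality inflate the error?** Not materially. Choosing between t-test and Mann-Whitney after a Shapiro test, at 63 per group and 4,000 runs, gave type I error 0.054 (rounded normal scores) and 0.056 (skewed scores). The single tests gave 0.053 to 0.056. What changes is the quantity compared.

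**5. Is power lost with the omnibus test?** It depends on the pattern of means (63 per group, SD 2).

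| Means (1, 2, 3) | λ | F-test power | t-test power, 3 versus 1 |
|---|---|---|---|
| 0, −0.5, −1 | 7.875 | 0.70 | 0.80 |
| 0, 0, −1 | 10.5 | 0.83 | 0.80 |
| 0, −1, −2 (stated difference) | 31.5 | > 0.999 | > 0.999 |

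There is no general loss. It appears for evenly graded means at half the stated difference.

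**The case against.** The strongest reply is that the quoted sentence already contains the right test. Group 3 versus group 1 is a two-group comparison, and the plan assigns a t-test or Mann-Whitney test to two groups. Nothing says that a significant F-test will be read as proof that 3 beats 1. This is also a journal article, and contrast order and multiplicity rules are commonly left to a fuller document.

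Much of this stands, and it rules out four stronger readings that a reader might infer:

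- **That no planned test controls the error.** A pre-named 3 versus 1 test does (step 3).
- **That false positives rise to about 12%.** Three unadjusted pairwise tests at 0.05 would give a familywise error of about 0.12, but the article does not plan them. With three groups, pairwise tests done only after a significant ANOVA gave 0.050 when all arms were equal.
- **That the normality switch inflates type I error.** The simulations show no material inflation (step 4).
- **That the plan loses power in general.** It does not (step 5).

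The absence of a multiplicity rule is not held against the article either. What the reply does not answer is that the article does state a rule. That rule is driven by the data, and it does not connect the test to the contrast on which the trial was sized. Medians with interquartile ranges are in PIPP-R points, as could be said in the plan's defence, but a rank test beside two medians still does not estimate a mean difference of 2 points.

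**Conclusion.** The point holds as a matter of designation and estimand. The hypothesis and the sample size rest on group 3 versus group 1, while the analysis section neither names that comparison as primary nor fixes its estimator. The 83% figure shows how little a significant omnibus test says about that contrast. It assumes normal data, SD 2, 63 per group and a 1-point benefit confined to group 2, and it describes the omnibus test only, not the error of a 3 versus 1 claim. The point about ranks applies only if the data are judged non-normal. The plan should be changed, but it does not follow that the trial is unable to answer its question.

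**What to change.** State in the analysis section that the single primary comparison is group 3 minus group 1 on PIPP-R. Estimate it as a mean difference with a 95% confidence interval and test it at two-sided 0.05, whatever the normality check shows. A linear model of PIPP-R on arm with robust standard errors would do; a hospital term is optional. Report Mann-Whitney as a sensitivity analysis in every case. Test 3 versus 2 and then 2 versus 1 in that fixed order, each only if the one before is significant, or label both as secondary.

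The cost is wording, with no extra infants or data. The downside is that no confirmatory claim can be made for the other contrasts if 3 versus 1 fails. The change should be fixed before anyone sees outcomes by arm.

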### Eligibility criteria

Healthy newborn infants, who will be screened with the routine newborn metabolic screening test and their parent are enrolled. Infants treated with sedatives or analgesics within the last 24 h are excluded. A written informed consent is acquired from the infant’s parents. Parents who understand Swedish or English are eligible for inclusion. The infant-parent dyad is randomly assigned to one of three treatment groups; one standard of care group with glucose (*n* = 75), one group with skin-to-skin contact (n = 75), and one group where skin-to-skin contact is combined with breastfeeding (if applicable) and live parental lullaby singing (n = 75), (Table 1).

**Table 1 Tab1:** Treatment groups

Group	Treatment	Treatment description
Group 1	Standard care with glucose	The infant is placed on the examination table for the blood test. Standard care comprises facilitated tucking done by a nurse or the parent, 1–2 ml of oral glucose (300 mg/ml) given in fractioned doses from 2 min before the procedure and the opportunity to suck on a pacifier or on a parent’s or a nurse’s plastic gloved finger.
Group 2a	Parent-driven pain management with skin-to-skin contact	The parent will sit in an adjustable recliner chair during the procedure and the infant will be placed naked (except for a diaper and possibly a hat) on the parent’s bare chest 10 min before the venipuncture. The skin-to-skin contact will proceed during and a while after the procedure.
Group 2b	Parent-driven pain management with skin-to-skin contact and breastfeeding	The parent will sit in an adjustable recliner chair during the procedure and the infant will be placed naked (except for a diaper and possibly a hat) on the parent’s bare chest 10 min before the venipuncture. Breastfeeding starts about 2 min before the venipuncture and the blood test is performed when the infant is latched and sucking well.

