Group 3	Parent-driven pain management with a combination of skin-to-skin contact, breastfeeding and live parental lullaby singing	The intervention in the combination group will follow the above described skin-to-skin and breastfeeding treatment descriptions. The parents are also instructed to hum a lullaby with their infant. The parent starts humming the lullaby when the infant is placed on the parent’s bare chest 10 min before the venipuncture and continues during and a while after the procedure. The humming should be performed in a simple, repetitive, soft and sedative mode in a low pitch, in consonant harmony, with a slow, steady and predictable pulse of 3/4 or 6/8 rhythm, maintaining a constant sound level between recommended ≤55–65 dB on the A-scale [49].

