### Interventions

The treatment groups in the RCT are described in Table 1. Group 2, comprising SSC, is divided into two subgroups, one with only SSC and one where the mother also chooses to breastfeed her infant during the test. The reason for these subgroups is that standard of care in one of the hospitals does not include glucose but comprises only SSC and breastfeeding when applicable. To ensure intervention fidelity in the live parental lullaby singing, a short video, showing a parent who sings according to the treatment description of the lullaby singing, will be played for the parents who are randomly assigned to group 3. These parents will also be verbally guided in how to sing before the intervention starts. The verbal instructions are simplified and delivered in dialogue with the parent who can ask questions.

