### Recruitment and allocation

The researcher in each region will present the study and provide written information about the study to eligible parents before they are discharged from the hospital (Fig. 1. Timeline SWEpap study). When the parent-infant dyads return to the postnatal care unit for the metabolic screening test, they will be asked to participate and to sign the consent form (both the mother and her partner). The parents who have accepted to participate are then randomly assigned to one of the three interventions groups using the sealed opaque envelope system with randomly generated treatment allocations administered by an impartial researcher. Once the parents have consented to enter the trial, the researcher opens the envelope and the allocated treatment regimen is offered to the parents. The researchers will then guide the parents in each group how to position themselves and the infant and if applicable how to use live parental lullaby singing. If the parent does not adhere to the protocol in the allocated treatment group, the infant will be excluded from the study.

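### Groups 2a and 2b are formed by the mother's choice and group 3 is not divided, so any comparison that uses the split is not randomised

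*Protocol article*

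**What the plan says.** The Study design section describes a trial "with three parallel groups with the allocation ratio 1:1:1". Recruitment and allocation confirms the unit of randomisation: "The parents who have accepted to participate are then randomly assigned to one of the three interventions groups". After consent the envelope is opened and the allocated regimen is offered.

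The Interventions section then divides group 2 into a part with skin-to-skin contact only (2a) and "one where the mother also chooses to breastfeed her infant during the test" (2b). The reason given is that "standard of care in one of the hospitals does not include glucose but comprises only SSC and breastfeeding when applicable".

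Group 3 has no such division, and it is described in two ways. The text under Eligibility criteria reads "one group where skin-to-skin contact is combined with breastfeeding (if applicable) and live parental lullaby singing". Table 1, in the same section, reads "The intervention in the combination group will follow the above described skin-to-skin and breastfeeding treatment descriptions", with no option stated.

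On how groups will be compared, the section Data analyses, management and monitoring says "The division of group 2 into 2a and 2b, which is a nomenclature to distinguish breastfeeding from no breastfeeding, will be taken into account". It adds that "differences between the two subgroups will be scrutinized". The same section states intention-to-treat with all randomised dyads. The Discussion concedes that the 2a/2b arrangement can be questioned. It defends it on the ground that mothers cannot ethically be stopped from breastfeeding, and it gives no analytic remedy.

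**The concern.** Randomisation protects comparisons between the three arms. It does not protect comparisons between parts of an arm that form themselves afterwards. Mothers who breastfeed during the blood test may differ from those who do not in ways related to the infant's response, such as how well feeding is established or which parent attends. The stated reason for the split is one hospital's practice, so 2a and 2b may also differ by site. The protocol nevertheless commits to using the split in the comparative analyses and does not mark the resulting contrasts as non-randomised.

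Group 3 adds a second difficulty. If some of its dyads do not breastfeed, it is also a mixture, yet only group 2 is separated. Comparing group 3 with 2b alone, or with 2a alone, then sets a whole randomised arm against a self-selected part of another.

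What is at stake is mainly the added value of singing, which the Discussion presents as the unexplored component. Group 2 is the only comparator from which that could be read.

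**Working it through.** The plan gives no figure on this point, so the check has two parts: what randomisation covers, and how large the effect of unequal breastfeeding could be.

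**1. Which contrasts are randomised**

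- Whole arms 1, 2 and 3 against each other: randomised, provided all randomised dyads are analysed.
- 2a versus 2b: not randomised. Membership follows the mother's choice. That the choice comes after allocation is an inference from the Interventions and Recruitment and allocation sections; the timing is not stated outright.
- Group 3 versus 2a alone, or versus 2b alone: not randomised, for the same reason.

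**2. What whole group 3 versus whole group 2 measures**

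Let S be the reduction in PIPP-R due to singing, B the reduction due to breastfeeding, and p2 and p3 the shares breastfed in groups 2 and 3. With additive effects:

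extra reduction in group 3 = S + (p3 − p2) × B

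The documents give no values for p2, p3 or B, so these are assumptions:

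- Equal uptake, p3 = p2: the extra term is 0 for any B.
- p3 = 1, p2 = 0.6: 0.4 × 1 = 0.4 and 0.4 × 1.5 = 0.6 points.
- p3 = 1, p2 = 0.4: 0.6 × 1 = 0.6 and 0.6 × 1.5 = 0.9 points.

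The next table gives the chance that a two-sided 5% t-test declares a difference when S = 0. It uses the SD of 2 and the 75 per group from the Sample size section.

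| p2 | p3 | B | Extra term | Chance of p < 0.05 |
|---|---|---|---|---|
| 0.5 | 0.5 | 1 | 0 | 5% |
| 0.7 | 0.8 | 1 | 0.1 | 6% |
| 0.5 | 0.8 | 1 | 0.3 | 15% |
| 0.5 | 1.0 | 1 | 0.5 | 33% |
| 0.7 | 1.0 | 2 | 0.6 | 45% |
| 0.3 | 1.0 | 1 | 0.7 | 57% |

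The extra term in points does not depend on the SD; the percentages do. The stated 63 per group does not follow from a 2-point difference with SD 2, which gives 16. It fits a 1-point difference with SD 2, or a 2-point difference with SD 4. That is a separate matter, but it makes the SD less certain.

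**3. Using one part of group 2 as comparator**

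The same formula with p2 = 0 (2a) gives an extra term of p3 × B. With p2 = 1 (2b) it gives (p3 − 1) × B, which is zero or works against singing. In both cases selection bias comes on top, and it cannot be sized from the document.

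**4. Precision of 2a versus 2b**

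The difference detectable with 80% power is (1.96 + 0.84) × 2 × √(1/n2a + 1/n2b). With 75 dyads in group 2:

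- Split 37/38: about 1.3 points; power for a 1-point difference is 57%.
- Split 60/15: about 1.6 points; power for a 1-point difference is 40%.

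So this comparison is both unprotected and imprecise.

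**The case against.** A reader might infer that the mother's choice confounds the group 3 versus group 2 comparison with singing, or that 2a versus 2b does so. The documents do not support either. Neither 2a nor 2b includes singing, so that contrast can only mix breastfeeding with maternal or site characteristics. Whole group 3 versus whole group 2 is randomised under the stated intention-to-treat analysis. Choice made afterwards does not bias it as a comparison of offered packages; unequal uptake changes only what the difference means.

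The protocol also names no group 3 versus group 2 contrast and does not say that such a difference would be credited to singing. The hypothesis and the sample size concern the combined package against standard care, that is, group 3 versus group 1, and the split does not touch that contrast. Nor may one assume that all of group 3 breastfeeds: one of its two descriptions makes breastfeeding conditional. All of this stands, and it limits the point.

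It can also be said that how the split is handled belongs in an analysis plan, and that the Discussion already admits the difficulty. This stands only in part. The article goes beyond silence: it commits to using the split in comparisons and to examining 2a/2b differences, and the Discussion's defence is ethical, not analytic.

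One qualification runs the other way. Recruitment and allocation says that infants of non-adherent parents are excluded, which conflicts with intention-to-treat. If Table 1 were read strictly, a group 3 dyad that does not breastfeed could be dropped while a group 2 dyad that does not breastfeed stays in as 2a. The protection of the whole-arm contrast therefore depends on intention-to-treat being the rule actually followed.

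**Conclusion.** The point holds in a limited form. Comparisons of 2a with 2b, and of group 3 with either part alone, are non-randomised and open to selection by maternal and site characteristics, and the protocol plans to use the split without saying so. Group 3 is not divided in the same way, and its two descriptions disagree on whether breastfeeding is optional.

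Whole group 3 versus whole group 2 is a valid randomised comparison of packages under intention-to-treat. As an estimate of the singing effect it carries an extra term that runs from zero (equal uptake) to 0.4–0.9 PIPP-R points under the unequal-uptake assumptions above. Those rest on assumed shares, an assumed breastfeeding effect and additivity. For scale, the Sample size section treats 2 points as clinically important for group 3 versus group 1, so the upper value is a little under half of that. The main powered contrast is not affected by the split.

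**What to change.** 1. In all three arms, before the envelope is opened, record whether the mother intends to breastfeed during the test. Record actual feeding in groups 2 and 3.
2. Keep arms 1, 2 and 3 as randomised for the main comparisons, with intention and site as covariates.
3. If the added value of singing is to be estimated, do it as group 3 versus group 2 among dyads whose mothers stated that intention before randomisation.
4. Label every comparison by actual feeding (2a/2b) as exploratory and non-randomised.
5. Reconcile the Eligibility criteria text with Table 1 on breastfeeding in group 3, and the exclusion sentence with intention-to-treat.

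None of this stops any mother from breastfeeding, so the ethical argument in the Discussion is respected. New envelopes stratified by intention are possible but not needed.

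The cost is one question at a stage when demographic data are already collected, plus changes of wording. The question must come before allocation; for dyads already randomised it cannot be recovered without bias. The stratum estimate is less precise. With SD 2 the difference detectable with 80% power is 2.80 × 2 × √(2/n): 0.9 points at 75 per arm, 1.2 at 45 per arm (60% intending) and 1.4 at 30 per arm (40% intending).

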### Study measures

The PIPP-R has been tested for reliability, construct validity and clinical utility, all with results indicating good psychometrics [50]. The PIPP-R evaluates three behavioral facial actions (brow bulge, eye squeeze and nasolabial furrow), two physiological items (heart rate, oxygen saturation), and two contextual items (gestational age and behavioral state). The PIPP-R gives a weighted and higher score for the youngest infants to adjust for their lesser ability to show signs of pain. Scores can range from 0 to 21 where a higher score signifies a higher level of rated pain. A PIPP-R pain assessment includes a 15 s baseline measurement of heart rate and oxygen saturation together with an observation of the infant’s behavioral state and gestational age. Changes in physiological and behavioral indicators from baseline are then assessed during the first 30 s of the painful procedure. PIPP-R scores will be assessed from video recordings after the procedure by a trained nurse and a subset will also be assessed by one of the researchers for interrater reliability [50].

Galvanic skin response (GSR) refers to changes in sweat gland activity in response to a sensory stimulus. GSR measurements detects changes in electrical (ionic) activity resulting from changes in sweat gland activity. The increase in skin conductance reflects the infant’s arousal intensity in response to the sensory stimulus. As an indicator of pain, skin conductance measurements have detected increased sweating in newborn infants < 28 + 0 postnatal age submitted to heel lancing [53]. GSR have been tested in several neonatal pain studies on term and preterm infants, measuring skin conductance that reflects pain-related activation of the sympathetic nervous system [52–55]. Analyses of GSR are presented with the following variables; area small peaks, area huge peaks (both representing forcefulness of sympathetic nerve firing), peaks per second (the rate of firing in the sympathetic nerves), average rise time, average peak. Higher values in any of the above GSR parameters are indicative of more stress [52].

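### Plain Cohen's kappa on the 0–21 PIPP-R score can substantially understate scorer reliability for the primary outcome; an ICC with limits of agreement suits the scale

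*Protocol article*

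**What the plan says.** Four parts of the protocol article bear on this point.

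- **Outcomes** makes PIPP-R primary: "The primary outcome is infant pain expression measured with Premature Infant Pain Profile Revised (PIPP-R").
- **Study measures** describes the scale: "Scores can range from 0 to 21 where a higher score signifies a higher level of rated pain". A trained nurse scores the video recordings, and "a subset will also be assessed by one of the researchers for interrater reliability". The size of that subset is not given.
- **Sample size** works in points on this scale: "a difference of two PIPP-R points between standard care (group 1) and the full parent driven pain management (group 3) is considered clinically important", and "Based on those studies we also assume a standard deviation around 2 points".
- **Data analyses, management and monitoring** opens with a general rule, "Methods for statistical analyses are chosen depending on scales of measurement and normal distribution", and then fixes the agreement statistic: "Cohens kappa will be used to calculate interrater reliability between PIPP-R scorers".

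The article mentions no weighting scheme, grouping of the score, item-level agreement analysis, ICC or limits of agreement.

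**The concern.** Cohen's kappa without weights is a statistic for nominal categories: two ratings match or they do not. The PIPP-R total has 22 ordered values, and the plan itself reasons about it in differences and standard deviations. Using a nominal statistic on such a score does not fit the section's own rule that the method follows the measurement scale.

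The double-scored subset is the only check the article describes on the scoring of the primary outcome, which relies on people rating video. Two things are at stake in how that check is reported. A pair of scorers who nearly always fall within one point of each other could be published with a kappa that readers take as weak agreement. And if kappa is low, the report would not show whether one scorer rates consistently higher or whether both are simply noisy.

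**Working it through.** The protocol gives no kappa value, reliability threshold or scorer error, so there is no figure of its own to reproduce. The check asks how far unweighted kappa departs from measures that respect the scale, under stated assumptions.

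**Inputs.** From the protocol: integer scores from 0 to 21, and an SD of about 2, used here as the spread between infants. Assumed: SD 4 (and 3) as a wider range; mean score 6 in part 1 and 5, 7 or 10 in part 2; scorer error SD of 0.4 to 1.0 points; exact agreement of 30 to 70%.

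**Formulas.** Unweighted kappa = (p_o − p_e)/(1 − p_e), where p_o is the proportion of exact matches and p_e the proportion expected by chance from the two scorers' marginal distributions. Weighted kappa = 1 − Σw·observed/Σw·expected, with w the squared distance between ratings for quadratic weights. Without a scorer shift, quadratic-weighted kappa and the ICC are both close to SD²/(SD² + error² + 1/12), where 1/12 is the variance from rounding to whole points.

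**1. True score plus independent scorer error** (400,000 simulated pairs, mean 6, no shift)

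| SD | Scorer error SD | Exact match | Within 1 point | Unweighted kappa | Quadratic-weighted kappa |
|---|---|---|---|---|---|
| 2 | 0.6 | 42% | 91% | 0.33 | 0.90 |
| 2 | 0.4 | 57% | 98% | 0.50 | 0.94 |
| 4 | 0.8 | 37% | 82% | 0.32 | 0.95 |

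Hand check of the first row: p_o = 0.423 and p_e = 0.134, so kappa = (0.423 − 0.134)/(1 − 0.134) = 0.289/0.866 = 0.33. The formula for the ICC gives 4/(4 + 0.36 + 0.083) = 0.90. For the second row, (0.568 − 0.137)/(1 − 0.137) = 0.50 and 4/(4 + 0.16 + 0.083) = 0.94.

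**2. Second scorer either matches exactly or differs by 1 point.** With mean 7 and SD 2:

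| Exact match | Unweighted kappa | ICC |
|---|---|---|
| 30% | 0.19 | 0.92 |
| 50% | 0.42 | 0.94 |
| 70% | 0.65 | 0.96 |
| 0% (every pair off by 1) | −0.15 | 0.89 |

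Across means of 5, 7 and 10 and SDs of 2, 3 and 4, kappa at 70% exact agreement is 0.65 to 0.69, against an ICC of 0.96 to 0.99. The gap narrows as exact agreement rises but stays in every case tried.

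**3. Systematic shift** (SD 2, mean 6)

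| Scorer error SD | Shift, points | Unweighted kappa | Quadratic-weighted kappa |
|---|---|---|---|
| 0.4 | 0 | 0.50 | 0.94 |
| 0.4 | 1 | 0.09 | 0.84 |
| 0.4 | 2 | −0.11 | 0.64 |
| 0.6 | 1 | 0.13 | 0.81 |
| 1.0 | 0 | 0.17 | 0.79 |

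Kappa does react to a shift. But the last two rows, one with a 1-point shift and the other with noisier scorers and no shift, give nearly the same kappa (0.13 and 0.17). Weighted kappa does not separate them either (0.81 and 0.79). Only a mean difference in points does.

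**The case against.** The strongest reply is that the text is underspecified rather than wrong. It does not say that kappa is unweighted or that it applies to the total. PIPP-R is built from seven items, and kappa per item would be reasonable. With weights or item-level use, most or all of the problem goes. An article also commonly leaves such detail to a fuller plan. This limits the point to the text as written, but does not remove it: kappa named without weights means the unweighted statistic, and what the article says is scored twice is the PIPP-R score, which it defines as 0 to 21. A method has been stated, so this is more than a gap.

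The size is also open to challenge. Gestational age and the filmed oximetry values leave little room for judgement. If scorers differ only on the three facial items (an assumption), 90% exact agreement per item gives 74% exact agreement on the total and kappa 0.71; 95% gives 0.84 and 85% gives 0.59. That stands: kappa could understate reliability badly or only moderately, and no document says which.

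A reader might infer two stronger things, and neither is supported.

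- *That a scorer shift would go unseen.* It would not: kappa falls from 0.50 to 0.09 under a 1-point shift. What it cannot do is identify the cause or give the size in points.
- *That a nurse–researcher difference bears directly on the 2-point target.* Nothing says the researcher's scores enter the treatment comparison. The nurse scores the recordings, muted and described as blinded, and the researcher rescores a subset for reliability only. A constant offset between the two does not bias a between-group difference in the nurse's scores.

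**Conclusion.** The point holds in a limited form. As written, the plan applies a nominal agreement statistic to an ordered 22-value score that it otherwise treats as quantitative. That statistic can substantially understate the reliability of the primary outcome's scoring: about 0.3 to 0.5 where a scale-appropriate measure gives 0.90 to 0.94 (SD 2, assumed scorer error 0.6 to 0.4), and about 0.65 to 0.7 if exact agreement is near 70%. It also cannot tell a systematic shift from random error.

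This rests on reading kappa as unweighted and applied to the total, and on scorer errors that the documents do not give. It would go too far to say that kappa will come out poor. Only the reported reliability is affected, and any distortion makes scoring look worse than it is; the treatment comparison, alpha and power are unchanged. It is worth correcting because the outcome is primary and the change is small.

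**What to change.** Replace the kappa sentence with one that states, for the PIPP-R total in the double-scored subset: a two-way, absolute-agreement ICC with 95% CI, and the mean difference between scorers with Bland–Altman limits of agreement in points. Keep kappa, with weights named, for the single ordinal items. If item-level or weighted kappa was intended all along, say so and add the ICC for the total. Limits of agreement by treatment group are optional.

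The cost is one sentence and a little more analysis. The same recordings and the same double-scored subset serve, with no new data and no burden on families.
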